### Recruitment

This cohort study aims to recruit at least 80% of the 1300 students and employees of BFH-DHP. The recruitment strategy comprised the following procedure: in consultation with and support of the director of BFH-DHP, an invitational letter will be sent via email to all students and employees during the first (April 2020) and second (May 2021) study periods.

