### Eligibility Criteria

All students (N=1300; 88% female and 12% male) enrolled in programs at the Bachelor of Science and Master of Science levels as well as all academic and nonacademic employees of BFH-DHP are eligible and will be invited to participate in this comprehensive, web-based survey. BFH-DHP runs these educational programs in the fields of nursing, nutrition and dietetics, midwifery, and physiotherapy. Individuals that are not employed or enrolled at the university will not be eligible for this study.

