#### Data Management

Data management will be performed on the BFH-DHP server. The EvaSys system will automatically store data collected from all study participants as comma separated variables (.csv) files. All data files will be imported and merged to a single data file in Excel (2018; Microsoft Corp).

Data cleansing will be performed by one researcher (JT) who will check and solve for example dot-comma decimal signs incompatibilities and to control plausibility of the data (ie, range checks). The iPAQ-SF data-cleansing guidelines will strictly be adhered to, that is, participants with incomplete (missing) data or those who responded “don’t know” will be removed from the analyses.

Data analyses will be carried out in 2 steps. First, data on physical activity, nutritional habits, alcohol consumption, and sleeping habits will be separately analyzed. Second, an explorative correlational analysis will be conducted, including only those participants with a complete set of data for all lifestyle habits under evaluation. Subgroup analyses will be conducted to compare differences in the outcomes between health profession divisions or between students’ academic levels (ie, BSc and MSc) and employee status.

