#### Statistical Analyses

Parametric and nonparametric statistics will be used to report results from both surveys and to compare survey results with reference values obtained from the general population during pre–COVID-19 conditions. For descriptive analyses, central tendencies will be expressed as means or medians, and variation will be expressed as SD and 95% CI or interquartile ranges (25th and 75th percentiles), respectively. Kruskal-Wallis tests with posthoc Bonferroni corrections will be used to assess differences between independent groups. Results will be presented as frequency tables or as figures with boxplots.

For the explorative correlation analysis, health profession divisions, students’ academic level, and employee status will be recoded as follows: nutrition and dietetics = 1, midwifery = 2, nursing = 3, physiotherapy = 4, BSc = 1, MSc = 2, and employee = 3. The Spearman rank order correlation coefficient will be used to assess associations between the different variables under analysis. Results will be presented in a correlation matrix.

Statistical analyses will be conducted using SPSS software (version 26.0; IBM Corp.). Statistical significance will be set at the 5% level of error.

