## Results

This longitudinal study was started during the lockdown in Switzerland, in mid-April 2020 and will be completed in May 2021. The first phase of the study is underway, and data from 823 participants will be evaluated.

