## Discussion

This paper outlines the study protocol of the survey conducted among BFH-DHP students and employees to evaluate their physical activity, nutritional habits, and sleep behavior during the 2020 COVID-19 confinement. This protocol has been developed as an interdisciplinary collaboration between faculty members of the Divisions of Nutrition and Dietetics and Physiotherapy.

During the same period, similar initiatives were undertaken by other institutes. For example, a large survey developed by a consortium of many international universities aimed to retrospectively evaluate the changes in lifestyle habits among the general population in context of the COVID-19 pandemic [2,15,16].

One of the strengths of our survey is that it will be short (time needed to complete the survey will be less than 10 minutes), limiting the questions to physical activity, nutritional habits, and sleep behavior within a specific setting of students and employees of BFH-DHP. We believe, this will help the participants place special focus on the current and future multipliers of healthy lifestyle habits and their own personal behavioral changes due to a general lockdown effected as a key countermeasure to combat the spread of the COVID-19 pandemic. Another strength of our survey is its prospective design over a 1-year period. Based on the large sample size comprising eligible staff and students (N>1500) and considering the huge impact of COVID-19–related strict measures on both the staff and students, we expect a reasonable response rate (ie, around 30%).
It may be hypothesized that such a confinement period may negatively affect physical activity levels of individuals, in general, and students and employees of BFH-DHP, in particular. In an effort to support the public in maintaining “healthy” physical activity levels, Swiss television channels resumed broadcasting home exercise programs after almost two decades. During this time, popular press reported an increase in the demand for fresh vegetables and fruit, as well as alcoholic beverages. Our survey will aim to verify and, if applicable, quantify such observations and put them in proper context.

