The results of this survey may have important public health impacts. They may empower heads of universities and higher education institutions to better prepare, inform, and counsel their students and employees on maintaining healthy lifestyle habits that may prove useful, for example, in case of an upcoming second wave of COVID-19 or a sudden outbreak of a serious new viral epidemic or pandemic in the future. Action plans for workplace health promotions may be developed with a special focus on digital dissemination routes to reach students and employees in their home-office settings.

Several biases can occur in cohort studies, which should be reduced. For instance, a selection bias resulting from the approach used to select or observe study participants, which may influence the relationship between exposure and outcome. To avoid this type of bias, this study will recruit persons from only a single institution, ie, BFH-DHP. Second, an information bias could originate either from the individuals being observed, observers, or instruments used to evaluate the results. In prospective cohorts, information bias can usually be easily avoided since measures can be taken during scheduling by including all variables in the registration forms (instruments) so that no variables of interest are overlooked.

Nevertheless, this study has limitations. The survey does not collect any data about illnesses among participants during the first phase, which could likely influence a change in the targeted behaviors.

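### Recruiting from a single institution does not avoid selection bias: in a voluntary survey of everyone, non-response does the selecting, and about 37% to at least 45% of those eligible are not in the 2020 analysis

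*Protocol article*

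**What the plan says.** The Discussion describes selection bias as arising from how participants are selected or observed, and then gives the remedy: "To avoid this type of bias, this study will recruit persons from only a single institution". The only limitation it goes on to name is the lack of illness data in the first phase.

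Under Recruitment and under Ethical Approval and Consent to Participate, all students and employees are invited by email and participation is voluntary. The Results section states that "data from 823 participants will be evaluated" from the first phase.

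The eligible population is given in three ways:
- Recruitment: the aim is to recruit "at least 80% of the 1300 students and employees of BFH-DHP", so 1300 covers both groups.
- Eligibility Criteria: "All students (N=1300; 88% female and 12% male", so 1300 is students alone and employees come on top.
- Discussion: "Based on the large sample size comprising eligible staff and students (N>1500", with an expected response of around 30%.

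Division, academic level and employee status are used as analysis variables. Data Management says "Subgroup analyses will be conducted to compare differences in the outcomes between health profession divisions", and Statistical Analyses gives the codes: "nutrition and dietetics = 1, midwifery = 2, nursing = 3, physiotherapy = 4, BSc = 1, MSc = 2, and employee = 3".

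**The concern.** Selection has two steps here: which population is approached, and who in it answers. Restriction to one institution concerns only the first step. It limits how far results generalise and leaves the second step untouched. Since everyone is approached, the second step is the whole selection mechanism. The survey covers exercise, diet, alcohol and sleep at a health-professions school, so it is plausible, though not shown, that willingness to answer is related to the answers.

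Three planned uses depend on this:
- **Overall estimates for the institution**, such as total activity and the low, moderate and high activity shares.
- **The comparison with general-population reference values** in Statistical Analyses. Self-selected members of one health-professions department may differ from those values for reasons unrelated to confinement, and restriction to one institution does not help this comparison.
- **Any contrast of 2020 with 2021.** The surveys are open for one week and two weeks respectively, so the mix of respondents may change between them.

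A reader who accepts the sentence in the Discussion would treat selection as dealt with in all three.

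**Working it through.** **1. The plan's own figures.** The article states no achieved response rate, so there is none to reproduce. The nearest figures are its two expectations:
- Recruitment: 0.80 × 1300 = 1040.
- Discussion: 0.30 × 1500 = 450.

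The 823 participants in the Results match neither, and the two expectations do not agree with each other.

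**2. Share of eligible persons not in the 2020 analysis**, m = 1 − 823/N:
- N = 1300: 823/1300 = 63.3%, so m = 36.7%.
- N = 1500: 823/1500 = 54.9%, so m = 45.1%. As N is given as above 1500, this is a lower bound. At an assumed N of 1600, m = 48.6%.
- On the Eligibility Criteria reading, N exceeds 1300 by an unstated number of employees, so m is above 36.7%.

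**3. Bias of an unweighted mean.** With d the respondent mean minus the non-respondent mean, bias = m × d. The number of institutions does not enter. Restriction changes only whom N counts. The documents give no value for d, so a range is assumed:

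| Assumed d (SD) | Bias, N=1300 (SD) | Bias, N=1500 (SD) |
|---|---|---|
| 0.1 | 0.04 | 0.05 |
| 0.2 | 0.07 | 0.09 |
| 0.3 | 0.11 | 0.14 |
| 0.5 | 0.18 | 0.23 |

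**4. Comparison with sampling error.** The 95% half-width of a mean is 1.96/√823 = 0.068 SD. If the target is the institution itself, the finite-population factor √(1 − 823/N) is 0.606 at N=1300 and 0.672 at N=1500, which gives 0.041 and 0.046 SD. At d = 0.2 the bias exceeds the half-width on either basis. At d = 0.1 it does not.

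**5. Proportions.** The largest half-width is 1.96 × √(0.25/823) = 3.4 points, or 2.1 to 2.3 points with the finite-population factor. If nothing is assumed about those not observed, the bounds on any prevalence are m wide, about 37 to 45 points. That is a logical limit, not an estimate of bias.

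**6. Change over time.** The error in a whole-survey contrast is (m × d in 2021) − (m × d in 2020). It cancels only if the two products are equal, and nothing in the design makes them so.

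**The case against.** The strongest reply is that only an article is shown. Weighting and non-response analysis are often left to a statistical analysis plan, and the sentence at issue sets no analysis rule. A reader might infer that the study makes no correction at all. The documents do not support that, since they show only that the article mentions none. The point therefore rests on the assurance itself, which an unseen plan cannot make true.

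Other parts of the reply also stand:
- The study takes real steps to raise response: everyone is invited, reminders are sent and the questionnaire takes under 10 minutes. Comparisons by division and status are planned, and those results do not depend on the division or status mix.
- A reader might infer that the counts needed for weighting are known. The variables are coded for respondents, but no eligible count per stratum is printed and even the total conflicts. That the department can supply the counts is an inference from its inviting everyone by email.
- Weighting by division and status cannot remove self-selection by lifestyle within a stratum, so it would not narrow the bounds in step 5 by much.
- If 823 is a count after the exclusions described under Data Management, the share that never took part is somewhat below 36.7% or 45.1%. The share missing from the analysis is unchanged.
- The section on Data Collection assigns the comparison of confinement with the later period to people who took part in both surveys, not to whole-survey contrasts. This weakens the concern over change in mix but does not remove it, because that subgroup is itself self-selected, twice over.

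**Conclusion.** The concern holds in this form: the sentence credits the design with a property it does not have. Of those eligible, 36.7% (N=1300) or at least 45.1% (N>1500) are outside the first-survey analysis. Under an assumed difference of 0.2 SD, the bias of an overall mean is 0.07 to 0.09 SD, as large as or larger than its sampling error.

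The shares rest on the document's own figures. The bias rests on an assumed difference and shows only what is possible. No passage shows that active people answered more often or that the mix of divisions differed between years. Two stronger readings should be resisted. The 37 to 45 point bounds do not measure the actual bias. A 70% unobserved share, inferred from the expected 30% response, does not apply to the first survey, which already has 823 participants; at most it is a scenario for the second.

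This should be changed because it limits what the study may conclude. It does not invalidate the study.

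**What to change.** 1. Delete the sentence. Say that restriction to one institution defines the population described, and that voluntary non-response limits the overall estimates, the comparison with reference values and any contrast of 2020 with 2021.
2. Reconcile the eligible totals in Recruitment, Eligibility Criteria and Discussion. State whether 823 is a count before or after data cleaning.
3. For each survey, tabulate respondents over eligible persons by division and by status (BSc, MSc, employee), assuming the department can supply the counts.
4. Show overall estimates post-stratified on these same variables in both surveys, beside the unweighted ones, with standard errors that allow for the weights. State that this corrects only for response differences between strata.
5. Add a sensitivity analysis that shifts the overall estimates by m × d for stated values of d, for example 0.2 SD.
6. For the comparison over time, do not add sex or age weights in 2021 alone. The first survey collected no sociodemographic data, so the two surveys would be weighted differently and become less comparable.

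The cost is a request for counts, a little more analysis work and slightly larger standard errors. No further data need be collected from participants.

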## Abbreviations

BFH: Bern University of Applied Sciences
bMDSC: brief Mediterranean diet screener
DHP: Department of Health Professions
iPAQ-SF: International Physical Activity Questionnaire-short form
